# Statistical analysis

Based on the published literature, we estimate that the no-needling and sham needling groups will improve on average by 20 VISA-A points after 12 weeks (due to the effects of exercise-based physiotherapy management),^25^ and we hypothesize that the IMS group will improve by a further 15 points (the minimum clinically significant difference).^42^ The SD of a single VISA-A score is 15^67^, and correlation between repeated measurements on the same patient after 1 week is 0.80.^67^ This makes the SD for the difference between 2 measurements on the same patient approximately 9.5. To detect these effects in a one-way ANOVA model with a residual standard deviation of 9.5 with power 95%, a sample size of 11 patients is needed in each group for a total of 33 patients. Assuming a 20% drop-out rate,^43^ 42 patients will initially be recruited and enrolled. The primary analysis will be a one-way Analysis of Variance with the response being the change in patients VISA-A score at 12 weeks. Secondary analyses will be performed on the change in patients VISA-A score at 6 months and 12 months from baseline, and on changes in dorsiflexion range of motion and global improvement scale. Inter-group post-hoc tests will be conducted in consultation with UBC statistical consulting services ([name], manager). Intention to treat analysis will be employed. If a clinically significant effect of IMS in Achilles tendinopathy exists, this pilot study has a 95% chance of successfully detecting it. If there is no clinically significant effect of IMS in Achilles tendinopathy, this study has a 95% chance of reaching this conclusion.

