**Is exercise an effective treatment?**

The strongest evidence (multiple, consistent, well controlled trials) supports heavy-load exercise as the cornerstone of managing AT. This form of exercise varies slightly from trial to trial, but the principal goal is to provide a strong, controlled, mechanical force to the Achilles tendon which is tolerable to the patient. This is usually achieved through eccentric (lengthening) muscle activity; for instance, a heel drop over a step. (In contrast, concentric exercise involves a toe raise that would contract the calf muscles.) As the patient’s tolerance of the exercise improves, the load is progressively increased (e.g., by progressing from bilateral to unilateral heel drops, by progressing the degree of dorsiflexion, by adding weights in a backpack or through use of gym equipment). Rompe and colleagues found this type of progressive, slow, heavy-load exercise to be superior to a wait-and-see strategy, with a 60% success rate in the exercise group (95% confidence interval [CI] 41%–79%) compared with 24% in controls who did not receive treatment (95% CI 7%–41%).^26^ Eccentric exercise was found to be superior to a standard exercise program in a multicentre randomized trial by Mafi and colleagues; 82% of the patients who trained with eccentric exercise were satisfied and had returned to their previous activity level after 12 weeks (95% CI 66%–98%), compared with 36% of patients who trained with standard (concentric) exercise (95% CI 16%–56%).^27^ Thus, eccentric exercise induces clinically meaningful effects but may take several weeks or months before a benefit is felt, and not every patient is guaranteed to respond. The potential harms of eccentric exercise include delayed-onset muscle soreness or exacerbation of the tendinopathy (e.g. pain, soreness or swelling). These typically occur when the exercises are performed too quickly, with incorrect biomechanics, or with an increase in load that is too abrupt. There are no published reports of tendon rupture in response to eccentric loading.

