**Extracorporeal shock wave therapy**

As for injection therapies, the current evidence for shock wave therapy as a treatment for Achilles tendinopathy is promising but inconclusive. Shock wave therapy involves the application of acoustic waves that vary in nature according to the type of device used and the amount of energy and energy flux delivered to the tissue. The evidence that met our criteria rested on two trials from the same group.^26 43^ One trial examined the effect of adding low energy (0.1 mJ/mm^2^) extracorporeal shock wave to a heavy-load eccentric exercise program. Patients who were randomly assigned to receive active shock waves plus exercise fared slightly better in terms of pain (1.5/10 improvement on a visual analogue scale; *p* = 0.0045), activity level (13.5/100 improvement on the VISA-A-A score; *p* = 0.016) and satisfaction with treatment at four months.^18^ Although statistically significant, these average values are rather small; the minimum clinically significant difference for the VISA-A-A score is 15/100, and for pain it is 2/10. However, only mean values were presented – the actual percentage of patients who achieved a clinically significant improvement in each group was not reported.

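### The 95% power for 12-week VISA-A change rests on a 1-week retest correlation and has almost no margin if the 12-week correlation is lower

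*Protocol*

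**What the plan says.** All the inputs are in the protocol's Statistical analysis section.

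- **Primary analysis:** "The primary analysis will be a one-way Analysis of Variance with the response being the change in patients VISA-A score at 12 weeks".
- **Expected change in the two control arms:** "the no-needling and sham needling groups will improve on average by 20 VISA-A points after 12 weeks".
- **Expected change with IMS:** "we hypothesize that the IMS group will improve by a further 15 points (the minimum clinically significant difference").
- **Variability:** "The SD of a single VISA-A score is 15", and "correlation between repeated measurements on the same patient after 1 week is 0.80". From these two figures the section obtains an SD of about 9.5 for the difference between two scores on one patient.
- **Use of that SD:** "To detect these effects in a one-way ANOVA model with a residual standard deviation of 9.5 with power 95" per cent, the section asks for 11 patients per group, 33 in all. It then enrols 42 to allow for 20% dropout.

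The section ends by giving the study, without any condition, a 95% probability of finding a clinically significant effect if one exists. The Limitations section repeats that the study is powered for clinically significant differences. Neither section gives a correlation or an SD of change over 12 weeks, or a range of power values.

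**The concern.** The interval behind the SD does not match the interval of the endpoint. Two scores taken a week apart differ mainly through measurement noise and short-term fluctuation. Two scores taken 12 weeks apart, with treatment in between, also differ because some patients improve more than others. That extra spread belongs in the residual SD of an ANOVA on change. Using the 1-week figure assumes, in effect, that all patients in an arm improve by nearly the same amount.

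The protocol does not itself hold that view. Its review of exercise treatment says that "not every patient is guaranteed to respond", and its Physical Examination section excludes patients without region-specific signs in order to limit variation in treatment response. The power calculation makes no allowance for such variation.

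The sample size, the stated power and the closing assurance all depend on this one input. If the trial is negative, a reader who trusts the 95% will take the result as near-conclusive evidence against a 15-point benefit. The trial may be able to say much less than that.

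**Working it through.** **Inputs.** From the Statistical analysis section: mean changes 20, 20 and 35 (20 + 15); single-score SD 15; correlation 0.80 at 1 week; 11 per group; 20% dropout; 42 enrolled. Assumptions: two-sided significance level 0.05 (not stated as such, but the plan's n reproduces with it), SD 15 at both time points, and equal arms.

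**Formulas.**
- SD of change = 15 × √(2 × (1 − r)), where r is the baseline-to-follow-up correlation.
- The grand mean is 25, so the squared deviations sum to 25 + 25 + 100 = 150.
- Noncentrality λ = n × 150 / SD². Power comes from the noncentral F distribution with 2 and 3(n − 1) degrees of freedom.

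**The plan's own figure.** 15 × √(2 × 0.20) = 9.49, which the plan rounds to 9.5. At SD 9.5, 10 per group give 94.1% power and 11 give 96.2%, so 11 is the smallest number reaching 95%. Dropout: 33 / 0.8 = 41.25, which rounds up to 42. Every stated figure reproduces.

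**Power at other 12-week correlations.** The protocol gives no 12-week value, so the rows below 0.8 are an assumed range. Eleven per arm is the plan's number of completers; 14 per arm is all 42 analysed.

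| 12-week r | SD of change | λ, 11 per arm | Power, 11 per arm | Power, 14 per arm |
|---|---|---|---|---|
| 0.8 | 9.49 | 18.3 | 96.2% | 99.0% |
| 0.7 | 11.62 | 12.2 | 85.4% | 93.5% |
| 0.6 | 13.42 | 9.2 | 73.4% | 84.5% |
| 0.5 | 15.00 | 7.3 | 63.0% | 75.2% |
| 0.3 | 17.75 | 5.2 | 48.1% | 59.7% |

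A simulation of 200,000 trials at SD 15 with 11 per arm gave 63.1%, in agreement with the exact value.

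**Margin.** With 11 per arm, power equals 95% at an SD of 9.82. Solving 15 × √(2 × (1 − r)) = 9.82 gives r = 1 − 9.82²/450 = 0.786. Any 12-week correlation below about 0.79 takes power under the stated figure. With 14 per arm the limiting SD is 11.21, so r = 1 − 11.21²/450 = 0.72.

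**The same point in terms of response.** Let true improvement vary between patients in an arm with SD s, independent of the 1-week noise, whose variance is 9.49² = 90. The SD of change is then √(90 + s²). With 11 per arm:

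| s (assumed) | SD of change | Power |
|---|---|---|
| 0 | 9.5 | 96% |
| 5 | 10.7 | 91% |
| 8 | 12.4 | 80% |
| 10 | 13.8 | 71% |

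The plan's figure corresponds to s = 0. A spread of 5 points around mean gains of 20 to 35 already takes power to 91%.

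**The case against.** The strongest reply is that nothing has been miscalculated. That is right: 9.5, 11, 33 and 42 all follow from the stated inputs. The fault is an input that does not fit the endpoint.

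A second reply is that any replacement figure is the reviewer's own. This also stands. A reader might infer that the true power is 63%, but that value needs a 12-week correlation of 0.5 and 11 analysed per arm, and the protocol gives no 12-week correlation. At 0.7 the loss is much smaller, and with all 42 analysed power is then 93.5%, close to the stated 95%. The protocol plans an intention-to-treat analysis without saying how dropouts enter it, so 11 and 14 per arm are best read as bounds.

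A third reply concerns outside support. The shock wave section reports a "13.5/100 improvement on the VISA-A-A score" with p = 0.016, and a reader might try to infer from this that the SD must exceed 9.5. The protocol gives no arm sizes for that trial. The implied SD runs from 8.1 at an assumed 6 per arm to 24.5 at an assumed 40, a range that includes 9.5. The outcome is also at four months, and the text does not say whether it compares changes or final scores. The check cannot be made. Likewise, the exercise section says only that response is not guaranteed; it gives no spread of VISA-A change.

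Finally, the study calls itself a pilot, and its conduct and primary test are unaffected. That bears on how large the remedy should be. It does not justify an unconditional power claim.

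**Conclusion.** The point holds as a mismatch between input and endpoint. The 95% power is correct for an SD of 9.5, but the protocol gives no ground for taking 9.5 as the SD of 12-week change under treatment. The figure has almost no margin with the planned 11 completers per arm.

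The direction is well supported, because variation in response can be expected to widen the spread of change. The size is not established. Over assumed 12-week correlations from 0.7 down to 0.3, the chance of missing a true 15-point benefit runs from about 15% to 52% with 11 per arm, and from about 6.5% to 40% with 14. These values assume SD 15 at both times, a 0.05 level, and control arms that improve equally.

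Two stronger readings are not supported. One is that the trial is shown to have 63% power, or any other single value. The other is that baseline adjustment already rescues the power. A baseline-adjusted model would have about 76% power at a correlation of 0.5 with 11 per arm (ignoring the covariate's degree of freedom), but the protocol specifies ANOVA on change, so that figure describes an analysis it does not contain.

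**What to change.** In the Statistical analysis section:

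1. State that 9.5 is derived from a 1-week retest correlation and that no 12-week correlation was available.
2. Replace the single 95% with a table of power for the specified ANOVA on change over a range of 12-week correlations labelled as assumed (for example 0.3 to 0.8), with columns for 11 and 14 per arm.
3. Delete the closing sentence that promises a 95% chance of detecting an effect, or make it conditional on the SD of change being 9.5. Qualify the matching remark under Limitations.

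Enrolment stays at 42. A baseline-adjusted power figure should be given only if the primary analysis is changed to adjust for baseline. The cost is wording only, with no extra patients and no change to conduct. The downside is that the stated power becomes less favourable.

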**[name]**

Conduct blinded ankle ROM assessments and deliver questionnaires to participants at entry into study, after 6 weeks of treatment, after 12 weeks of treatment and 1 year after entry into study.

Direct participants in completing questionnaires ie participant to enter study ID # and time point in study (entry into study, after 6 weeks of treatment, after 12 weeks of treatment and at 1 year after entry into study)and deliver to front desk for storage in locked cabinet.

Remain blinded to participant allocation. Report patient unblinding.

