**Outcome measures**

The primary outcome measure for which the study is powered is the 12 week VISA-A score - a well validated and reliable disease-specific outcome measure, which also includes an activity-related pain scale.^67^ Secondary outcome measures include treatment success/failure, and muscle length (dorsiflexion ROM). Patients will rate themselves from 0 (very much worse) to 6 (very much improved). Scores of very much improved or much improved will be categorized as successes.^68^ Dorsiflexion range of motion with knee bent and straight will also be measured using an inclinometer, giving an indication of the effect of IMS and exercise vs exercise alone on muscle extensibility. These measures will be taken at 0 and 12 weeks, as well as at 52 weeks.[[1](#_ENREF_1)] After 12 weeks and 6 months of intervention, UTC scanning will be conducted to determine, as a pilot study, whether there is any subjective indication of a potential effect of IMS on tissue remodeling that could be pursued with a mechanistic study in future.

Muscle length measures will be made according to the protocol described by Norkin and White^69^ and Kendall and colleagues^70^ by a physiotherapist (MB) unaware of the treatment allocation. The two-joint plantarflexors (gastrocnemius and plantaris) will be measured in supine with the knee extended. The one-joint plantarflexors will also be measured in supine but with the hip and knee flexed 90 degrees or more to make the two-joint plantar flexors slack across the knee joint. The ankle will be passively dorsiflexed and the angle achieved measured by goniometry. The fulcrum will be centred over the lateral aspect of the lateral malleolus, the proximal arm will be aligned with the lateral midline of the fibula, using the head of the fibula for reference, and the distal arm will be positioned parallel to the lateral aspect of the fifth metatarsal. The ankle will be dorsiflexed to end-of-range (firm muscular end-feel) by pushing upward across the plantar surface of the metatarsal heads, without allowing the foot to rotate into inversion or eversion. Intratester reliability in measuring passive ankle dorsiflexion by goniometry has been shown to have an Intraclass Correlation Coefficient (ICC) of 0.91 for more experienced therapists.^71^ MB has had over three decades of musculoskeletal clinical experience.

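### The primary ANOVA on raw 12-week VISA-A change has no baseline VISA-A term; an ANCOVA would be at least as efficient, apart from small estimation costs, and would remove chance baseline imbalance from the estimate

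*Protocol*

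**What the plan says.** Outcome measures defines the endpoint: "The primary outcome measure for which the study is powered is the 12 week VISA-A score". Statistical analysis then fixes the model: "The primary analysis will be a one-way Analysis of Variance with the response being the change in patients VISA-A score at 12 weeks". A one-way model has a single factor, the treatment group, and the protocol names no covariate anywhere.

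The planning values are in the same section. For the controls, the "no-needling and sham needling groups will improve on average by 20 VISA-A points after 12 weeks". For the active arm, "we hypothesize that the IMS group will improve by a further 15 points (the minimum clinically significant difference". The variability inputs are "The SD of a single VISA-A score is 15" and "correlation between repeated measurements on the same patient after 1 week is 0.80". From these the protocol derives a change SD of about 9.5, 11 patients per group for 95% power, and 42 enrolled to allow for 20% drop-out.

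Scientific rigor deals with baseline balance. Once half the patients are enrolled, one researcher compares the groups on symptom duration, gender, age and baseline VISA-A, and later randomisation may be weighted. The stated analysis does nothing about any imbalance that remains.

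**The concern.** Subtracting baseline amounts to assuming that the 12-week score rises one point for each baseline point. When the true slope is below 1, subtraction over-corrects: an arm that starts lower by chance will appear to gain more. The model also carries more residual noise than one that estimates the slope from the data.

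With 11 to 14 patients per arm, chance differences in mean baseline can be several points. The protocol regards baseline VISA-A as important enough to inspect and possibly to re-weight the randomisation, yet the primary model does not use it as a predictor. At stake are some power and a removable error in the one trial that will be run.

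**Working it through.** **Inputs.** From Statistical analysis: mean changes 20, 20 and 35 (20 + 15); SD of a single score 15; r = 0.80 over one week; 11 per group. Assumed: two-sided alpha 0.05 (the protocol states none), the same SD of 15 at both times, and hence a baseline slope equal to r.

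**The protocol's own figure.** Change SD = 15 × sqrt(2 × (1 - 0.80)) = 9.49, which matches 9.5. The grand mean is 25, so the squared deviations sum to 25 + 25 + 100 = 150. Noncentrality at n = 11 is 11 × 150 / 9.5² = 18.3 on 2 and 30 df, giving power 96.2%. At n = 10 power is 94.2%. So 11 is the smallest n that reaches 95%, and 33 / 0.8 = 41.25 rounds up to 42 (14 per arm). The sample size reproduces.

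**Change score against ANCOVA.** Change SD = 15 × sqrt(2(1 - r)). ANCOVA residual SD = 15 × sqrt(1 - r²). The variance ratio is (1 - r²) / (2(1 - r)) = (1 + r)/2. At r = 0.80 the ANCOVA SD is 15 × 0.6 = 9.0 and the ratio is 0.90. Power uses the noncentral F distribution, with one error df fewer for ANCOVA (29 in place of 30 at n = 11). Only the first row uses a correlation from the protocol.

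| r | Change SD | ANCOVA SD | Variance ratio | Power at 11 per arm, change | Power at 11 per arm, ANCOVA | n per arm for 95%, change / ANCOVA |
|---|---|---|---|---|---|---|
| 0.80 (protocol, 1 week) | 9.49 | 9.00 | 0.90 | 96.2% | 97.6% | 11 / 10 |
| 0.70 (assumed) | 11.62 | 10.71 | 0.85 | 85% | 91% | 15 / 13 |
| 0.60 (assumed) | 13.42 | 12.00 | 0.80 | 73% | 83% | 20 / 16 |
| 0.50 (assumed) | 15.00 | 12.99 | 0.75 | 63% | 76% | 25 / 19 |

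The ANCOVA column is slightly favourable, because it ignores the variance added when the slope is estimated with unequal baseline means. With 33 patients in three arms that inflation averages about 1/(30 - 2) = 3.6%. The variance ratio is then nearer 0.90 × 1.036 = 0.93 at r = 0.80, and 0.75 × 1.036 = 0.78 at r = 0.50. The ordering does not change.

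**Imbalance carried into the estimate.** Given a baseline difference D between two arms, the change-score contrast is shifted by (1 - r) × D in size, in the opposite direction to D. The standard error of D is 15 × sqrt(2/11) = 6.4 points at 11 per arm and 15 × sqrt(2/14) = 5.7 at 14.

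- D = 6.4 (one standard error): a shift of 0.2 × 6.4 = 1.3 points at r = 0.80, and 0.5 × 6.4 = 3.2 at r = 0.50.
- D = 10: a shift of 2 points at r = 0.80, and 5 points at r = 0.50, against a target of 15.

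A difference of 10 or more between one given pair of arms has probability of about 12% at 11 per arm (10 / 6.4 = 1.56 standard errors) and about 8% at 14 per arm.

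**The case against.** The strongest reply is that the planned analysis is sound on the protocol's own figures. The change-score contrast is unbiased over randomisations and the test is valid. The stated 95% power is met without adjustment, and ANCOVA gains 1.4 percentage points, or one patient per arm. The larger gains rest on correlations that the protocol does not give. The fall from 96% to 63% at r = 0.5 comes mainly from using a one-week correlation in the sizing. That is a separate matter, and ANCOVA only partly offsets it (76%). The mid-recruitment balance check is also some protection.

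All of this limits the size of the point but does not remove it. The balance check acts only on later allocation, once 21 of the 42 are enrolled, and leaves the estimate unadjusted. If allocation is weighted because of baseline VISA-A, that is a further reason to put it in the model. ANCOVA also helps most where the planning correlation proves too high.

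A reader might also infer that the plan drops every patient without a 12-week score and so contradicts "Intention to treat analysis will be employed". The text does not support this. Inflating 33 to 42 is ordinary sizing and sets no exclusion rule. The protocol states no analysis set or missing-data rule, and such a rule is commonly left to the SAP, which is not at hand. No drop-out bias can be computed from the document either.

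**Conclusion.** The point holds as a modest, specific improvement to a stated choice. The primary model omits a baseline measurement that is planned for every patient and that the protocol itself treats as important for balance.

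At r = 0.80 the cost of the omission is about 10% in residual variance, 1.4 percentage points of power, and 2 points of shift for a 10-point imbalance. At an assumed r of 0.5 it is 25%, 13 percentage points and 5 points. These figures rest on alpha 0.05, equal SDs of 15 and a linear baseline relation. The imbalance is error conditional on the realised allocation, so it should not be read as systematic bias. Nor do the figures show the trial to be underpowered on its own assumptions.

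**What to change.** State the primary analysis as an ANCOVA of the 12-week VISA-A score with group as factor and baseline VISA-A as covariate, and keep the one-way ANOVA on change as a sensitivity analysis. This also matches the endpoint as Outcome measures words it. With baseline in the model, the group contrasts are the same whether the response is the score or the change. The cost is one error degree of freedom and a sentence of protocol text, settled before outcome data are examined by group. No new data, visits or patients are needed.

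A mixed model that also uses the 6-week VISA-A is an option only once the visit schedules agree. Study Team and Roles has questionnaires delivered "at entry into study, after 6 weeks of treatment, after 12 weeks of treatment and 1 year after entry into study", Outcome measures lists 0, 12 and 52 weeks, and Statistical analysis refers to VISA-A at 6 months. These need to be reconciled first.

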## Study Team and Roles

**[name]**

Conduct initial phone screen (with [name] and [name]).

After final eligibility screen by [name] and informed consent obtained, consult random number generation table and record subject group allocation, ensure confidentiality of files (must be in a locked cabinet accessible only by the study team).

Collate initial subject files and deliver to locked cabinet at Kinetic clinic.

Prepare patient exercise diary with appropriate dates filled in.

Collect hard copies of data (VISA-A forms and Global Improvement forms completed by study participants, ankle ROM forms completed by MB, treatment attendance data logged by LS) from locked cabinet at Kinetic and enter into Master Tracking Sheet on password-protected computer.

Monitor patient flow through study, ensure all appointments are booked and confirmed when they happen, including assessment by MB and UTC scans by LS, as per Master Tracking Sheet.

Maintain unblinding log.

Contact participants re 1 year follow-ups.

Send de-identified data (e.g. copies of Master Tracking Sheet) to [name] or designate upon request.

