**[name]**

Oversee recruitment strategy, distribution of posters and study materials. Conduct initial phone screen (with [name] and [name]).

Conduct physical assessment screen.

Obtain informed consent. (Documents to be stored in locked cabinet at Kinetic for collection by HD).

Create tracking sheet for ankle range measures, VISA-A questionnaires (n= 4 x 42 = 168), Global Improvement scales (n= 4 x 42 = 168), and unblinding sheets for [name] and deliver to locked cabinet at Kinetic.

Collect ultrasound tissue characterization (UTC) images.

Interpret UTC images (with [name]).

Provide dry needling and exercise treatments and progressions.

Report unexpected events (per UBC Nov 11 2012 policy) to [name].

Track study expenditures.

Remain blinded to VISA-A / Global Improvement scores / ROM scores.

Record patient attendance dates and store in locked cabinet for [name] to access and record on Master Tracking Sheet.

Ensure data stored securely.

Deliver data from Canopy to Kinetic for collection by HD.

Primary contact in case of adverse event.

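### A secondary analysis of VISA-A change is planned at 6 months, but no assessment described in the protocol collects VISA-A at that time

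*Protocol*

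**What the plan says.** Four places in the protocol bear on when VISA-A and the global improvement scale are measured.

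- **Statistical analysis** sets the primary analysis on the 12-week change in VISA-A and then adds: "Secondary analyses will be performed on the change in patients VISA-A score at 6 months and 12 months from baseline". The same sentence goes on to further secondary analyses "on changes in dorsiflexion range of motion and global improvement scale".
- **Study Team and Roles, entry for the blinded assessor**, has ankle range of motion measured and questionnaires given out "at entry into study, after 6 weeks of treatment, after 12 weeks of treatment and 1 year after entry into study".
- **Study Team and Roles, entry for the treating physiotherapist**, sets the number of forms to prepare: "VISA-A questionnaires (n= 4 x 42 = 168), Global Improvement scales (n= 4 x 42 = 168").
- **Outcome measures** says: "These measures will be taken at 0 and 12 weeks, as well as at 52 weeks". Its only 6-month item is imaging: "After 12 weeks and 6 months of intervention, UTC scanning will be conducted".

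The coordinating role under Study Team and Roles has one later follow-up task: "Contact participants re 1 year follow-ups".

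Outcome measures describes the global scale as a seven-point self-rating (0 to 6) that runs from marked worsening to marked improvement. The top two categories count as treatment success.

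**The concern.** An analysis section can only use scores that the schedule produces. Here it names a 6-month VISA-A change, and none of the descriptions of data collection includes a 6-month VISA-A. A later statistical analysis plan cannot repair this, because a questionnaire not given at 6 months cannot be recovered. If the mismatch stays, someone must decide later whether 6 months meant 6 weeks, was abandoned, or was collected ad hoc. In a three-arm trial of 42 participants, that choice should not be made with results in view.

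The global improvement scale raises a related point. Each score already expresses change since entry, so a rating at entry has nothing to describe. Four forms per participant are nevertheless planned, one of them at entry, and the wording of the analysis section can be read as taking a change in that rating. Nor does that section name the success/failure outcome that Outcome measures defines.

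**Working it through.** **Step 1. Reproduce the planned number of forms.** The inputs are the four questionnaire times in the assessor's entry (entry, 6 weeks, 12 weeks, 1 year) and the 42 participants to be enrolled.

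Forms = times × participants = 4 × 42 = 168.

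This equals the stated figure for each instrument, so all four forms are taken up by the assessor's schedule and none is left for 6 months. With a 6-month VISA-A the count would be 5 × 42 = 210, which is 210 − 168 = 42 more than planned.

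**Step 2. Set the times for VISA-A side by side.**

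| Time | Assessor's schedule | Outcome measures | Statistical analysis |
|---|---|---|---|
| Entry / 0 weeks | yes | yes | baseline |
| 6 weeks | yes | no | not named |
| 12 weeks | yes | yes | primary |
| 6 months | no | tissue scan only | secondary |
| 1 year / 52 weeks | yes | yes | secondary |

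The 6-month row has an analysis and no collection. The 6-week row has collection in one place and none in the other. If the sentence on times in Outcome measures is taken to cover range of motion alone, the two sections still conflict at 6 weeks, because the assessor's schedule covers range of motion as well.

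**Step 3. The global improvement scale.** The planned count is again 4 × 42 = 168, which includes one form per participant at entry. Without the entry form it is 3 × 42 = 126.

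If an entry rating X were subtracted from a later rating Y, the variance would be

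Var(Y − X) = Var(Y) + Var(X) − 2 Cov(X, Y).

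- If every participant marks the no-change point at entry, X is constant, Var(X) = 0 and nothing is added.
- If X is unrelated to Y and equally variable (an assumption), Var(Y − X) = 2 Var(Y), so the variance doubles.

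The protocol gives no figure that places the result between these two cases.

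**Step 4. Does this reach the primary analysis?** The sample size rests on the 12-week change alone.

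- SD of change = 15 × √(2 × (1 − 0.80)) = 9.49, stated as about 9.5.
- With mean changes of 20, 20 and 35, SD 9.5 and a two-sided 5% level (assumed, since the protocol states none), the three-group ANOVA has power 0.941 at 10 per group and 0.962 at 11 per group. The stated 11 is therefore reproduced.
- Enrolment: 33 / 0.80 = 41.25, rounded up to 42.

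No input here depends on the 6-week, 6-month or global-scale questions.

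**The case against.** The strongest reply is that this is a slip of one word. If 6 months was written for 6 weeks, no analysis lacks data, the 6-week scores have a use, and the form count already fits. That is plausible, but the protocol does not say so, and it does name a 6-month visit for scanning, so a reader cannot tell which was meant. The contradiction stands, while the likely simplicity of its cause argues against a high severity. The flow chart is not available in the text reviewed. A 6-month VISA-A shown there would conflict with the form count and with both descriptions of collection.

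Three stronger readings are tempting, and the document does not support them.

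- *The 6-week score is wasted.* The protocol names no analysis of it, but a separate statistical analysis plan may do so. Its absence here is evidence that the time points are mismatched and is not an omission in its own right.
- *The plan subtracts a meaningless entry rating from the global scale.* No passage states a subtraction. The word for change in the analysis section may apply to range of motion only, and Outcome measures defines success by the category reached, which points away from subtraction. What does stand is that an entry form is planned for a scale that rates change, and that the analysis section leaves its use unclear.
- *The treatment-success comparison loses precision.* The added variance could be anything from none to a doubling, so no loss can be claimed.

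The protocol also requires the therapist who scans and treats to stay blinded to VISA-A. Adding the questionnaire at the 6-month scan visit is therefore not free of consequences.

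**Conclusion.** The protocol contradicts itself on the secondary time points. A 6-month VISA-A change is to be analysed, yet none of the 168 planned forms falls at 6 months, so as written this analysis has no data. Its sections also disagree on whether 6 weeks is a measurement time. This conclusion rests on the form count and on two separate descriptions of the schedule, and it assumes only that the flow chart does not overrule all three.

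The global-scale point is real but softer. An entry rating is planned where there is nothing yet to rate, and the analysis section should say plainly that the outcome is success or failure at the times after entry.

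The effect is confined to secondary outcomes. The 12-week primary analysis, the 11 per group and the 42 enrolled are untouched. Severity is moderate: a planned analysis that cannot be run must be reconciled, but the main conclusion of the trial does not depend on it.

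**What to change.** Put the two entries under Study Team and Roles, Outcome measures and Statistical analysis on one schedule before any data are seen. There are two ways to do it.

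1. **If 6 weeks was meant:** change 6 months to 6 weeks in Statistical analysis and add 6 weeks to Outcome measures. The 168 VISA-A forms stand.
2. **If 6 months was meant:** add a 6-month VISA-A to the schedule, giving 5 × 42 = 210 forms, and settle whether 6 weeks is a measurement time in Outcome measures. The form should be self-completed and returned to the front desk for the locked cabinet, as the assessor's entry already arranges at other times, so that the therapist who scans and treats does not see it.

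Under either option, drop the entry global improvement form (126 forms if the other three times are kept). State in Statistical analysis that the scale is analysed as the success/failure outcome of Outcome measures at times after entry, with no baseline subtraction. The choice of test can be left to the statistical analysis plan.

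The cost is wording in four places. The planned total for the two instruments is 168 + 168 = 336 forms. Option 1 needs 168 + 126 = 294, which is 42 fewer. Option 2 needs 210 + 126 = 336, no net change, plus the handling arrangement at 6 months. The sample size stays as it is.
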